### Assessment of microcirculation

The sublingual microcirculation will be assessed at the Kilifi site only using incident-dark field (IDF) imaging (CytoCam, Braedius Medical BV
^®^). IDF orthogonal polarization spectroscopy imaging technology is a validated real-time visualization of the microcirculation using a 2ms pulsed green light emitted at a 530nm wavelength for optimal optical absorption by the haemoglobin in red blood cells, independent of oxygenation state. It is safe, non- invasive and can be performed rapidly at the patients’ bedside. A sterilised disposable lens is used to prevent contact between the instrument and patient and therefore to prevent any transmission of infection. Two trained individuals will collect this data to limit inter-user variability. Images will be recorded from the proximal, mid, and distal portions in each halfof the sublingual mucosa and averaged. Where possible the microcirculation will be assessed at time 0 (prior to sevuparin dose), at 8–9 hours (before and after infusion) and again at 17–18 hours (after final dose). The image acquisition and analysis used for assessment of the microcirculation will be in line with the 2018 consensus agreement. This will include a Capillary Network Analysis for vessel densities (total and perfused), the proportion of perfused vessel and the average perfusion speed indicator.

### Additional laboratory investigation

At 1- and 8- hours and Day 28 plasma and red cell pellets will be used measure of the level Plasmodium falciparum Histidine Rich Protein (plasma). In addition the presence of rosetting and detailed microscopic examination of the infected red-cell morphology to stage the maturity of the parasite (Kilifi site only).

## Trial outcome measures

### Primary outcomes

APTT>2.5xULN 1h post any sevuparin dose (grade 3 following the CTC)

### Secondary outcomes

Change in lactate from 0 to 8 hours

Presence of mature infected erythrocytes on the blood films at 8 and 24 hours

Parasite clearance time

(Change in sublingual microcirculation over time)

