## Objectives

### General objectives

The primary objective of this trial is to conduct a dose-finding study of intravenous sevuparin given in 3 doses over the first 18 hours from enrolment (within 24h of hospital admission), defining toxicity events as any APTT >2.5 upper limit of normal (ULN) (grade 3 toxicity) 1 hour after each dose to identify the maximum tolerated dose (MTD). The initial dosage (1.5 mg/kg) and the
*a priori* dose- toxicity curve are based upon the results of the adult trial (where a dose of 1.5 mg/kg was associated with minimal risk of toxicity) and experimental evidence of dose-dependent efficacy i.e. inhibition of merozoite invasion and reversal of cytoadherence of infected erythrocytes
^
42
^. Almost all adults enrolled in this trial experienced grade 2 toxicity after one or more sevuparin doses, but APTT rapidly normalized, hence the choice of grade 3 toxicity to define the MTD in this dose-finding trial.

The primary endpoint for the future Phase II trial reflects the primary hypothesis that Sevuparin improves microcirculatory flow by reversing and preventing parasite sequestration. Data collected in the Phase I trial will also assess whether lactate clearance at 8-, 16- and 24 hours is a realistic and feasible primary endpoint for a subsequent Phase II trial.

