### Specific objectives

To identify the maximum tolerated dose (MTD) of intravenous sevuparin as an adjunctive therapy in children with severe malaria given as three infusions at 0, 8 and 16 hours using the Continual Reassessment Method (CRM) to adapt or inform subsequent doses for each child entering the trial, based on a toxicity event defined as any APTT >2.5 upper limit of normal (ULN) 1 hour after each dose, and updating the dose-toxicity model using the previous patients’ APTT results. The secondary objective will be to assess whether lactate clearance at 8 hours is a realistic and feasible primary endpoint for a subsequent Phase II trial.

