### Inclusion criteria

1.   Aged between 3 months and 12 years admitted to the paediatric wards within the last 24h

2.   Current evidence of
*P. falciparum* malaria (slide positive)

3.   Clinical evidence of severe malaria: impaired consciousness: coma (inability to localize painful stimulus) or prostration (inability to sit unsupported for those above 6 months) or deep breathing

4.   Lactate > 2 mmol/L

5.   Guardian or parent willing and able to provide consent

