### Clinical assessments

Members of the clinical team and study team will all receive pre- and peri-trial training on the management of severe malaria. A manual of operations for the trial will be available for the study team, to anticipate and troubleshoot any potential issues. Vital signs will be monitored regularly (including temperature, heart rate, respiratory rate, blood pressure, oxygen saturation, conscious level). These will continue twice-daily after 24 hours until the child is discharged from HDU. All children will be managed on the HDU until conscious and able to take and retain oral fluids/food. During the period of sevuparin administration (0–24 hours) children in Kilifi, Kenya will have continuous electrocardiogram (ECG) monitoring for safety. However, it is notable that the trial in Thai adults showed no signs of QT prolongation
^
42
^. Once discharged from HDU children will be reviewed daily until discharge and followed up at day 7 and day 28. On admission and Day 28 children will be assessed by an adapted Kilifi Developmental Index to assess developmental status and clinically for neurodevelopmental sequelae (see
Table 2). Non-compliance is limited by the intervention being administered by clinical teams during admission. Any child who develops APTT>2.5xULN (grade 3 toxicity) will not receive further doses of sevuparin but will continue to be followed up. Children lost to follow-up before day 28 will be traced for vital status (permission requested within consent) using locator data and multiple contact phone numbers recorded before discharge.

**Table 2. T2:** Clinical management schedule.

	Assessment Time										
Procedure	Adm	1h	2h	4h	8h	9h	17h	24h	Bi daily to discharge	Day 7	Day 28
Clinical assessment	X	X	X	X	X			X	X	X	X
ECG continuous to 24 hours (Kilifi)	X							X			
APTT and coagulation tests (ACT) (1.7ml)	X	X 1 hr post dose				X 1 hr post dose	X 1 hr post dose	X			
Microperfusion ^ & ^	x					x	x				
Lactate (point of care)	X	X				X		X			
Standard clinical test non-research (FBC, POC chemisty Istat) *	X								X		X
Malaria slides	X					X		X	(36,48, 72 hrs)	X	X
Stored red cells & admission plasma **	X					X					X
PK sample		X				X					
Neuro-developmental assessment	X										X

^&^ Kilifi Site only

* Standard- non research clinical tests full blood count, clinical chemistry POC iSTAT (electrolytes, pH BUN) will be done at admission and at 24 hours and Day 7 (Full blood count only).

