Other laboratory test: venous blood gases (including base excess) will be done at 0, 9 and 24 hours

Malaria slide and morphology will be done at 0, 9, 17, 24, 36, 48 hours (and 72 hours if in hospital); at follow up (Day 7 and 28)

**For quantitative plasma HRP2 assessment, biomarkers and parasite morphology (Kilifi site only)

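### The 0 to 8 hour lactate outcome has no scheduled 8 h sample: Table 2 takes lactate at admission, 1, 9 and 24 h, and the 9 h value follows the second infusion

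*Protocol article*

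**What the plan says.** All references are to the protocol article.

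- **Secondary outcomes** lists "Change in lactate from 0 to 8 hours".
- **Specific objectives** gives one secondary objective: "The secondary objective will be to assess whether lactate clearance at 8 hours is a realistic and feasible primary endpoint".
- **General objectives** is wider: the data will "assess whether lactate clearance at 8-, 16- and 24 hours is a realistic and feasible primary endpoint for a subsequent Phase II trial".
- **Discussion** says that the Phase II trial plans to use the change in lactate at 8 h as its primary endpoint, and that this trial will test whether that is feasible.
- **Table 2** (Clinical assessments), in the row beginning "Lactate (point of care", has marks under Adm, 1h, 9h and 24h only. The 8h column carries a clinical assessment and nothing else. There is no 16h column, and the 17h column has no lactate.
- **Notes to Table 2** follow the same pattern: "venous blood gases (including base excess) will be done at 0, 9 and 24 hours".
- **Trial treatments** times the three infusions at 0, 8 and 16 h after enrolment.
- **Inclusion criteria** allow children "admitted to the paediatric wards within the last 24h".
- **Additional laboratory investigation** takes samples "At 1- and 8- hours and Day 28 plasma and red cell pellets" for HRP2. Table 2 places the stored samples at Adm, 9h and Day 28.

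**The concern.** The lactate objective exists to find out whether an 8 h lactate is a workable primary endpoint for the next trial. A schedule that never takes that measurement cannot answer the question directly: it gives no completeness rate, no distribution and no variance for the 8 h value.

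The obvious substitute, the 9 h sample, differs in kind as well as in time because it comes after another infusion. The SEVUPARIN section reports that in adults the changes in circulating parasite forms appeared within one hour of the first injection. A sample one hour after dose 2 may therefore already reflect that dose. The choice of 8 h also has a stated basis: the section on pathophysiology cites failure to clear lactate at 8 h as strongly associated with death at 72 h (odds ratio 4.62, 95% CI 2.7 to 8.0).

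**Working it through.** The plan gives no sample-size or power figure for lactate, so there is nothing to reproduce. The check compares the times that the text requires with the times that are scheduled.

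**Step 1. Is the table read correctly?** Its columns are Adm, 1h, 2h, 4h, 8h, 9h, 17h, 24h, twice daily to discharge, Day 7 and Day 28. The APTT row, read by position, falls at Adm, 1h, 9h, 17h and 24h. Its cells marked as one hour post dose land at 1, 9 and 17 h, which is right for doses at 0, 8 and 16 h. The alignment is sound, and the prose note on blood gases independently gives 9 h.

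**Step 2. Required against scheduled.**

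| Measurement | Times in the text | Times in Table 2 or its notes | Missing |
|---|---|---|---|
| Lactate | 0, 8, 16, 24 h | Adm, 1, 9, 24 h | 8 h, 16 h |
| Films for mature infected erythrocytes | 8, 24 h | 9 h and 24 h among others, none at 8 h | 8 h |
| HRP2 / red cells | 1 h, 8 h, Day 28 | Adm, 9 h, Day 28 | 1 h, 8 h |

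Scheduled 8 h lactates: 0 per child × 20 children = 0. The same holds for 16 h.

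**Step 3. Nearest substitutes.** For 8 h the nearest lactate is at 9 h, and 9 − 8 = 1 h after dose 2. For 16 h the nearest are 9 h (16 − 9 = 7 h early) and 24 h (24 − 16 = 8 h late). Neither can stand in for 16 h.

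**Step 4. How much does one hour matter by itself?** The documents give no rate of lactate decline. As an illustration only, assume first-order decline with half-life h, so that the fall by time t is 1 − 0.5^(t/h).

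| Assumed h | Fall by 8 h | Fall by 9 h | Difference |
|---|---|---|---|
| 4 h | 75.0% | 79.0% | 4.0 points |
| 8 h | 50.0% | 54.1% | 4.1 points |
| 12 h | 37.0% | 40.5% | 3.5 points |
| 24 h | 20.6% | 22.9% | 2.3 points |

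Under these assumptions the clock shift alone is worth about 2 to 4 percentage points, which is modest. The larger matter is that the 9 h value includes exposure to dose 2. The documents give no means of sizing that.

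**The case against.** The case for leaving this alone has several parts.

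- **A usable change exists.** A 0 to 9 h change can be computed for every child, and 24 h, one of the three times in the General objectives, is scheduled. The Assessment of microcirculation section describes an 8 to 9 h assessment before and after infusion that Table 2 shows only under 9h, so for that measurement the column stands for a short visit window. This is fair: the defect lies in the outcome as defined, and an early lactate change is not lost. But no such window is stated for lactate, and none covers 16 h.
- **Nothing says that the outcome isolates the first dose.** That is correct, and the point does not need it. It is enough that the 8 h label and a sample one hour after dose 2 describe different exposures.
- **The stakes are limited.** The trial is single-arm, has 20 children across several doses, and describes its endpoints without testing them. No dosing decision uses lactate. All of this stands.

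A reader might go further and infer that the baseline lactate could be up to 24 h old, because doses are timed from enrolment, enrolment may follow admission by up to 24 h, and the baseline column is headed Adm. On that reading much of any apparent clearance would precede the drug. The documents do not support it. The Abstract and the Discussion equate admission with 0 hours. The notes to Table 2 label the baseline gas and slide as 0. The microcirculation section puts its time 0 reading before the dose, and Table 2 files that same reading under Adm. The natural meaning of Adm is the zero of the dosing clock. The wording is loose and worth tightening, but it is no evidence of bias.

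**Conclusion.** The text and the schedule contradict each other. As defined, the 0 to 8 h lactate outcome has no scheduled observation in any of the 20 planned children, and neither does the 16 h time. What the schedule delivers is a 0 to 9 h change taken one hour after the second infusion. The film times and the HRP2 and red-cell times show the same mismatch.

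This affects the only stated secondary objective and the information passed to Phase II. It does not touch the primary outcome, the dose-toxicity model or the maximum tolerated dose. Lactate should not be called the key secondary endpoint: the article uses that description only for APTT at 24 h. The conclusion rests on Table 2 as published. The 2 to 4 point figure rests on assumed half-lives and is illustrative.

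**What to change.** 1. Schedule a point-of-care lactate at 8 h, immediately before the second infusion. Alternatively, redefine the outcome as the change from 0 to 9 h, state that it is post-dose-2, and carry that wording through the objectives and the Phase II plan.
2. Add a 16 h lactate to Table 2, or delete 16 h from the General objectives.
3. State that the Adm or time 0 lactate is the one taken just before the first infusion.
4. Reconcile the film times and the HRP2 and red-cell times with Table 2, in whichever direction is intended. The blood gases need not move to repair the lactate outcome.

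**Cost.** The 9 h draw must stay, because the one-hour-post-dose APTT and the PK sample are taken then. An 8 h lactate is therefore an additional sampling occasion: one small point-of-care sample per child (at most 20 in all), and a second at 16 h if that time is kept (at most 40 in all). The sampling limit in the Safety section continues to apply.

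**Timing.** The Trial status section shows Kenya halted and Nchelenge not yet open, so the amendment could precede enrolment there. Children already enrolled may have only the 9 h value. Keeping the 9 h lactate alongside the new 8 h one would let the two groups be described on a common time.

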### Safety endpoints

APTT 24h post enrolment (absolute level and grade)

Development of abnormalities of coagulation indices (prothrombin) (Grade 2 and above)

Neurological sequelae through day 28

Mortality through day 28

Serious adverse events through day 28

Grade 3/4 adverse events through day 28

APTT 24h post enrolment will be used as an assessment of normalization 8h after the final sevuparin dose. Both absolute levels and grade will be considered.

De-novo evidence of neurological sequelae will be ascertained using a modified Kilifi Developmental Index
^
63
^ assessed at admission (to identify pre-existing conditions) and follow up (which we have adapted to use for the other trials.

Serious adverse events will use the standardized definitions (see section 11 below). SAEs will be independently reviewed in real-time by the DMC. Adverse events will be graded following the Common Toxicity Criteria v5.0: (
https://ctep.cancer.gov/protocoldevelopment/electronic_applications/docs/CTCAE_v5_Quick_Refe rence_5x7.pdf).

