### Adjuvant or supporting treatments aiming at improving the microcirculation

The demonstration in autopsy studies of microvascular obstruction by a heavy parasite burden
^
28
^ and that an overall measure of parasite biomass (
*Plasmodium falciparum* histidine-rich protein2 (pfHRP2), a protein released on sequestration by infected erythrocytes), correlates with worse outcomes
^
29
^ suggest that adjuvant therapies which can reverse sequestration and reduce overall biomass (by preventing merozoite invasion) early in the course of the disease may lead to substantial improvements when the risk of fatal outcome is highest. Moreover, the time of development of a merozoite into an adhesive infected erythrocyte that sequesters and blocks the micro-vasculature is
^~^18–20 hours which is the same time period (first day of hospitalization) when the majority of paediatric deaths from severe malaria in Africa occur.

In studies conducted in Indonesia, it was hypothesized that heparin could inhibit
*P. falciparum* sequestration and merozoite invasion since heparin binds to heparan sulphate binding structure of
*Plasmodium falciparum* erythrocyte membrane protein 1 (PfEMP1), the Duffy-binding like domain 1α (DBL1α), known as a vital contributor to sequestration of infected erythrocytes
^
30,
31
^. Clinical trials showed that heparin, as an adjunctive therapy to antimalarial drugs, had variable results, with some showing reduced mortality in children with severe
*P. falciparum* malaria
^
32,
33
^, others showing no clinical improvements when given as a low dose
^
34
^ and others demonstrating potentially severe effects on coagulation in simian studies in
*P. knowlesei* malaria at the same dosage as those showing benefit in children with severe malaria
^
35,
36
^. As a result, heparin was not subsequently adopted into clinical practice owing to the substantial concern over haemostatic side effects. Subsequent investigation has shown that that the inhibitory effect of heparin on
*P. falciparum* sequestration and merozoite invasion (which also is mediated through the heparan sulphate binding site of PfEMP) is independent of its anti-coagulant activity
^
37,
38
^. The next step was to develop a heparin compound that was devoid of its therapeutic limiting effects on coagulation.

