In the Phase I dose escalation trial, sevuparin was found to be safe and well-tolerated with minimal effects on APTT at doses of 1.5 mg/kg and 3mg/kg every six hours but a dose of 6.0 mg/kg led to higher APTT values. The Data Monitoring Committee (DMC) therefore recommended that the study should continue to the Phase II with a dose of 3.0 mg/kg sevuparin every 6h, given the potentially increased risk of adverse events at higher doses
^
42
^.

In the Phase II trial, sevuparin was administered as an intravenous infusion over 5 minutes in addition to standard care i.e., a fixed dose combination of 1000 mg atovaquone and 400 mg proguanil once daily for three days, in subjects with uncomplicated
*P. falciparum* malaria (experimental arm), as compared to atovaquone/proguanil treatment alone (control). There were minimal and non-clinically relevant changes in anti-Xa- and prothrombin-times, and the international normalized ratios associated to the sevuparin dose. Increases in APTT were dose-dependent and appeared to follow the time-concentration curve for each sevuparin infusion. The 6-hour interval between the infusions allowed for nearly full reversibility of APTT levels after each dose, and no accumulative effects were seen over the course of the 12 consecutive infusions. Thrombocytopenia occurred in one subject but was noted to be present before the initiation of sevuparin treatment. There was no incident of bleeding in any of the participants nor were there any other serious adverse events or adverse events
^
42
^.

Sevuparin was therefore judged to be safe and well tolerated in adults with mild malaria and was found to safe with minimal side effects in other clinical trials
^
43
^. It led to a reduction in numbers of ring-stage infected erythrocytes after a single sevuparin infusion and resulted in a transient appearance of mature parasite infected erythrocytes (schizonts appearing in the circulation, indicating these had been released after desequestration). These both occurred within one hour after the first sevuparin injection. Thus, these studies indicate that a novel new drug candidate for adjunctive treatment of severe malaria had been identified that blocks merozoite invasion and transiently de-sequesters infected erythrocytes in humans with uncomplicated
*P. falciparum* malaria.

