## Sampling

### Sample size determination

This is a Phase I trial designed to obtain data on safety, dosing, feasibility, and lactate clearance of sevuparin given as an adjuvant therapy in severe malaria. We aim to study 20 children since this will allow sufficient data on safety to be generated across a range of doses to identify the maximum tolerated dose (MTD) from a more informed model relating dose to toxicity events (denoted the ‘dose- toxicity’ curve) than that available
*a priori* based on published data from adult studies. After each patient is enrolled, the dose-toxicity curve will be updated based on levels of APTT taken over three time points (1h post each infusion), defining a toxicity event as APTT >2.5xULN at any time point (grade 3 following the Common Toxicity Criteria (CTC)). This enables the MTD to be estimated more rapidly using the Continuous Reassessment Method (CRM)
^
59
^ once determined, subsequent participants will be allocated to this MTD to provide the most accurate estimate of future toxicity event rates until we reach the sample size of 20 children. However, the CRM method will continue to use information from all these children; for example, if a number of children receiving the originally identified MTD experience toxicity events, the dose would again be lowered, and future children would receive this lower dose.

**
*Sampling procedures and methods.*
** Children admitted to the paediatric wards of in Kilifi and Nchelenge Hospital children with suspected malaria and either coma or deep breathing (defining severe malaria for this Phase I study) will be screened by the paediatric triage/admission team for eligibility. Once eligibility is verified, the parents can be approached for consent and, if they agree to participate, they will receive their allocated treatment dosage. The blood tests taken at admission and during the trial include standard of care and research bloods (see

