Table 2). Admission and serial assessment of full blood count, admission point of care clinical chemistry including PH, blood cultures and repeated assessment of malaria parasitaemia are part of the standard clinical tests. Additional to this will be serial assessment of lactate, measurements of coagulation (by iSTAT (Kaolin ACT) and laboratory-based APTT) and samples will be stored in Kilifi for future pharmacokinetic (PK) tests, plasma HRP2 tests and malaria parasites(research). The reliability of Point of care ACT measurements (using the iSTAT) have previously assessed against a laboratory gold standard and have shown that the coefficients of variation of POC ACT and whole blood were between 2% and 3.6%, indicating that POC assessments are reliable and able to support on-site decision-making for patients in acute and intensive care
^
60
^.

Management and outcome data will be collected (clinical parameters and recovery, developmental assessment, number of transfusions, use of drugs (specifically anticonvulsants, paracetamol, and antibiotics), date of discharge or in-hospital death. Contact and locator data will be recorded so that children can be followed at day 7 and day 28.

**
*Consent process.*
** Once eligibility has been confirmed, authorized trial staff will approach parents/guardians to invite their child to take part in the trial. An information sheet will be provided to the parent/guardian in their usual language. The sheet will be read aloud to those who are unable to read. The doctor/nurse will check that the information has been fully understood and parents/guardians will be encouraged to ask questions they may have about their child’s participation.

Where possible, prospective written informed consent will be sought from parents/guardians by asking them to sign the Consent Form. If parents/guardians are unable to sign, a thumbprint will be taken in lieu of a signature. A copy of the Consent Form will be given to the parent/guardian, the original placed in the patient’s medical notes, and a copy kept in the Investigator Site File.

If it is considered that the full consent process would significantly delay enrolment, and consequently be detrimental to the child’s health, then emergency verbal assent, used in previous trials
^
61

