^, will be sought from parents/guardians by the admitting medical team. Following verbal assent, written informed consent will be sought from the parent as soon as possible once the child’s clinical condition has stabilized.

The participant information sheet, consent form and case report files can be found as
*Extended data*
^
62
^.

**
*Trial treatments.*
** We aim to study 20 children (See
Figure 1 Trial Flow). The trial will be open label with clinicians aware of study drug dosage. Laboratory staff performing APPT levels will be blind to drug dosage. All children will receive standard care including parenteral artesunate. Sevuparin will be given as three infusions at 0, 8 and 16 hours after enrolment. The initial participants (two ‘cohorts’ of 2 children each, i.e., 4 children in total) will receive a dose of 1.5 mg/kg/dose with the plan to escalate up to the next highest dose up to a maximum of 6.0 mg/kg/dose for subsequent children. In order to determine whether, and the rate of escalation, to move to a higher dosage for subsequent patients after the first 4 children we will use a design called the Continuous Reassessment Method (CRM). This starts with an
*a priori* dose-toxicity curve, reflecting the probability of experiencing a toxicity event (here APTT>2.5xULN 1h after any of the three doses) to the dose received. In this method of dose finding, the dose-toxicity curve is re-fitted to the data after each child is enrolled, based on their observed dose and whether they had a dose limiting toxicity event. After the first 4 children, each subsequent patient would be assigned the next highest dose, until the estimated risk of toxicity is just below or at the target toxicity level, designated as the maximum tolerated dose (MTD). The dose limiting toxicity (grade 3 APTT, >2.5xULN),
*a priori* dose-toxicity curve and chosen target toxicity rate (15%) used in this trial have been based upon data shared by the investigators from the adult sevuparin studies in Thailand [36]. In particular, almost all adults enrolled in this trial experienced grade 2 toxicity after one or more sevuparin doses, but APTT rapidly normalized, hence the choice of grade 3 toxicity to define the MTD in this dose-finding trial. APTT 24h post-enrolment is a key secondary safety endpoint to confirm rapid normalization.

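### Non-serious grade 1-2 bleeding, the clinical counterpart of the APTT prolongation that drives escalation, is not a required safety result

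*Protocol article*

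**What the plan says.** All references are to the protocol article.

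- **Primary outcomes:** "APTT>2.5xULN 1h post any sevuparin dose (grade 3 following the CTC").
- **Safety endpoints:** "APTT 24h post enrolment (absolute level and grade"), abnormal prothrombin from grade 2 upwards, neurological sequelae, mortality and serious adverse events, each of the last three through day 28, and "Grade 3/4 adverse events through day 28". Grading follows CTC version 5.0.
- **Secondary outcomes:** lactate change, mature infected erythrocytes, parasite clearance and sublingual microcirculation. None is a bleeding measure.
- **Sampling procedures and methods:** management and outcome data include "number of transfusions, use of drugs". Table 2 schedules full blood counts. Neither transfusions nor platelet count is listed as an endpoint.
- **Statistical analysis:** clinical data are to be summarised, and the primary and secondary endpoints described. Safety endpoints are not mentioned by name.
- **Adult evidence (SEVUPARIN):** "There was no incident of bleeding in any of the participants". One thrombocytopenia was present before treatment.
- **Sample size determination:** "We aim to study 20 children since this will allow sufficient data on safety to be generated".

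**The concern.** The DLT is set at grade 3 APTT because grade 2 prolongation was nearly universal in the adult trial and resolved quickly. The Justification for the study adds that the adult APTT effects had no clinical consequences. For a prolonged APTT, the consequence that matters is bleeding. The trial carries that premise into severely ill children. They are excluded for platelets only below 25 ×10⁹/L, thrombocytopenia is described as common in severe malaria, and the planned range reaches 6.0 mg/kg/dose. Yet the endpoint list gives no means of testing the premise below grade 3.

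The thresholds are also uneven. A laboratory marker (prothrombin) counts from grade 2, while the clinical event it stands for counts only from grade 3 or if serious.

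The results are meant to contribute to the question of safety in severe malaria (National and international policymakers). A report of no grade 3/4 bleeding would be read as reassurance. It also could not be set against the adult finding of no bleeding at all, because lower-grade bleeds need not appear in it.

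**Working it through.** **Figure in the plan.** The sample size of 20 is justified in words. No formula, power or a priori curve is printed, so there is nothing to reproduce, and no stated figure is contradicted. The check is of endpoint content, with supporting arithmetic.

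**Step 1: where each haemostatic event would be counted.**

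| Event | Listed endpoint |
|---|---|
| APTT >2.5×ULN 1 h after a dose | primary outcome |
| APTT at 24 h, level and grade | safety endpoint |
| Prothrombin abnormality, grade 2 and above | safety endpoint |
| Bleed, grade 3/4 or serious | adverse event or SAE endpoint |
| Bleed, grade 1-2, not serious | none |
| Platelet change below grade 3 | none (blood counts scheduled) |
| Transfusion | none (number collected) |

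**Step 2: what zero severe bleeds could exclude.** With 0 events in n children, the exact one-sided 95% upper limit is 1 − 0.05^(1/n).

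- All 20 children: 1 − 0.05^(1/20) = 13.9% (two-sided, 1 − 0.025^(1/20) = 16.8%).
- The first 4 children, all at 1.5 mg/kg/dose: 1 − 0.05^(1/4) = 52.7%.

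**Step 3: chance of seeing at least one event in 20**, from 1 − (1 − p)^20. The article gives no bleeding rate, so every p below is an assumption.

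| Assumed true rate p | Calculation | Chance of at least 1 in 20 |
|---|---|---|
| 1% | 1 − 0.99^20 | 18% |
| 2% | 1 − 0.98^20 | 33% |
| 5% | 1 − 0.95^20 | 64% |
| 10% | 1 − 0.90^20 | 88% |
| 20% | 1 − 0.80^20 | 99% |

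If severe bleeding runs at 1-2%, the grade 3/4 line is more likely than not to show no bleed. If any-grade bleeding runs at 10-20%, events would very probably occur, and those below grade 3 and not serious would enter no endpoint.

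**Step 4: comparison with the laboratory measure.** At the 15% target toxicity rate, treating all 20 children as if at that rate, 1 − 0.85^20 = 96% for at least one APTT event, and every such event is counted.

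**The case against.** A reader might infer that haemostatic harm would go largely unreported. The article does not support that. The primary outcome is itself haemostatic, two safety endpoints are coagulation measures, SAEs are reviewed in real time by the DMC, and a child with a DLT is followed until APTT resolves. Only non-serious, low-grade clinical events are left out.

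A reader might also take bleeding to be a known harm of sevuparin. The statement that "heparin was not subsequently adopted into clinical practice owing to the substantial concern over haemostatic side effects" is about heparin. For sevuparin, the article reports that the antithrombin-binding sequence was removed, that APTT rose with dose, and that no bleeding occurred.

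Nor does the plan forbid reporting low-grade events. Statistical analysis says clinical data will be summarised, and Trial treatments calls APTT at 24 hours a secondary safety endpoint, so the omission of safety endpoints from the analysis sentence may only be condensed wording. The CRFs are not shown, so low-grade bleeding may already be recorded.

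Platelet and transfusion measures are weak evidence here. There is no control group, thrombocytopenia is common in malaria, and transfusion follows haemoglobin thresholds. Change from admission does not separate drug effect from disease.

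All of this stands, and it narrows the point. It does not remove it. The article states the grade threshold for clinical events, so the threshold is not a detail left to a fuller document, and as stated it leaves low-grade bleeding out of the required results.

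**Conclusion.** The point holds as a moderate, cheaply mended weakness in endpoint definition, not as an error in a figure. Non-serious grade 1-2 bleeding is not a required safety result, while the laboratory measures and severe or serious bleeds are captured.

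The endpoint gap and the 13.9% and 52.7% limits rest on the article and arithmetic alone. Those limits would apply to any endpoint with no events in 20 or in 4 children. The contrast between 18-33% and 88-99% rests wholly on assumed bleeding rates of 1-2% and 10-20%. At an assumed 5% for any-grade bleeding, the chance of seeing an event is 64%. Whether low-grade bleeding is already on the CRF cannot be judged from the article. If it is, only the endpoint list needs changing.

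**What to change.** 1. Add to Safety endpoints: bleeding events of any grade through day 28, tabulated by dose received, with exact confidence limits.
2. State in Statistical analysis that the descriptive analysis covers the safety endpoints.
3. Optionally list alongside, as description only, platelet count at the scheduled full blood counts (change from admission) and transfusions after the first infusion. Note that without a control group these cannot be separated from the course of malaria.
4. Reconcile the full blood count times. As the table reads in the available text, the Table 2 grid marks admission, the bi-daily column and day 28, while its footnote gives admission, 24 hours and day 7.

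**Cost:** a few lines of wording, one small table and slightly more event recording, with a CRF entry if none exists. Some low-grade events will reflect the disease rather than the drug. Items 1 to 3 need no additional children or procedures. Nothing here implies a change to dose, DLT definition or stopping rules.
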